## Abstract

Pharmacologic cardioversion is a well-established alternative to electric cardioversion for hemodynamically stable patients, as it skips the risks associated with anesthesia. A recent network meta-analysis identifies the most effective antiarrhythmics for pharmacologic cardioversion with flecainide exhibiting a more efficacious and safer profile towards faster cardioversion. Moreover, the meta-analysis of class Ic antiarrhythmics revealed an absence of adverse events when used for pharmacologic cardioversion of AF in the ED, including patients with structural heart disease. The primary goals of this clinical trial are to prove the superiority of flecainide over amiodarone in the successful cardioversion of paroxysmal atrial fibrillation in the Emergency Department and to prove that the safety of flecainide is non-inferior to amiodarone in patients with coronary artery disease without residual ischemia, and an ejection fraction over 35%. The secondary goals of this study are to prove the superiority of flecainide over amiodarone in the reduction in hospitalizations from the Emergency Department due to atrial fibrillation in the time taken to achieve cardioversion, and in the reduction in the need to conduct electrical cardioversion.

## 1. Introduction

Atrial fibrillation (AF) is the most frequent heart arrhythmia in the adult population [1]. This is reflected in the number of ED visits with a primary diagnosis of AF, as well as in the high percentage of admissions due to AF [2,3]. According to the current data, the annual number of visits to the Emergency Department due to atrial fibrillation continues to rise [4]. Hospital admissions related to atrial fibrillation also tend to increase, increasing the financial burden to the national health system [5]. It has been proven that interventional programs at the ED can reduce admissions due to AF and the associated costs [6,7,8]. In this setting, prompt cardioversion of atrial fibrillation at the Emergency Department has been independently proven to significantly reduce admissions and the related costs [9], as well as its progression to persistent atrial fibrillation [10], and the serious cardiovascular risks associated with it [11]. Data from Italy [12] and the USA [4] show that the percentage of patients coming to the ED and subsequently becoming hospitalized is much higher than the percentage of patients coming to the ED for any diagnosis and then hospitalized. Furthermore, it is noteworthy that the majority of these patients that visited the ED with AF had a calculated CHA2DS2-VASc score ≥ 2 and were already under optimal anticoagulation. Therefore, these patients could theoretically be submitted to cardioversion at the Emergency Department and could possibly be discharged.

Pharmacologic cardioversion is a well-established alternative to electric cardioversion for hemodynamically stable patients as it skips the risks associated with anesthesia [13,14]. However, the current guidelines do not prioritize between antiarrhythmic agents and do not take into account the time taken to restore the sinus rhythm [13,14,15].

Antiarrhythmic drugs, such as amiodarone, flecainide and propafenone, are considered as the primary choice for hemodynamically stable patients. In patients without structural heart disease, the use of intravenous flecainide or propafenone is recommended, while for patients with a history of heart failure or SHD, amiodarone is the drug of choice. A recent network meta-analysis identifies the most effective antiarrhythmics for pharmacologic cardioversion with flecainide exhibiting a more efficacious and safer profile towards faster cardioversion. Moreover, the meta-analysis of class Ic antiarrhythmics revealed an absence of adverse events when used for pharmacologic cardioversion of AF in the ED, including patients with structural heart disease. 

Over the last years, the importance of ‘time-consuming’ pharmacological cardioversion of AF was depreciated in favor of electrical cardioversion. ED cardioversion as a management approach for stable patients with recent-onset AF potentially allows for discharge directly from the ED, and, thereby, may be advantageous towards health care resource allocation, cost, and potential patient satisfaction perspectives. We hypothesize that using flecainide for the cardioversion of eligible patients will allow for faster cardioversion times, while maintaining the same or a better safety profile than amiodarone.

## 2. Objectives

The primary goals of this clinical trial are to prove the superiority of flecainide over amiodarone in the successful cardioversion of paroxysmal atrial fibrillation at the Emergency Department and to prove that the safety of flecainide is non-inferior to amiodarone in patients with coronary artery disease without residual ischemia and an ejection fraction over 35%. The secondary goals of the study are to prove the superiority of flecainide over amiodarone in the reduction in hospitalizations from the Emergency Department due to atrial fibrillation in the time taken to achieve cardioversion, and in the reduction in the need to conduct electrical cardioversion. A successful cardioversion is defined as the restoration of the sinus rhythm, documented by a 12 lead ECG lasting at least 1 h. 

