### 3.4. Sample Size

In our meta-analysis, we estimated the pooled cardioversion rate by flecainide within 4 h 65% whereas by amiodarone 23% (17). Taking 65% as our point estimate, the steering committee of FLECA-ED considers that flecainide can be regarded as non-inferior to amiodarone in patients with ischemic cardiomyopathy if the lower margin of the confidence interval does not go lower than the pooled rate (65%) by more than 20% (i.e., if it is not lower than 45%). Based on these assumptions, we expect that a sample size of 96 patients per arm is required to achieve 80% power to demonstrate the efficacy of flecainide in these patients, when a type I error rate is set at 0.05. Given the close follow-up of our patients in our registry, we do not expect a substantial dropout rate and thus aim to recruit a total of 200 (100 per arm) patients.

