### 3.7. Outcomes

The study’s primary endpoints are the frequencies of successful cardioversion within 6 h of drug administration as well as the combined frequency of PVCs, NSVT, SVT, bradycardia and hypotension during the same time frame. The main secondary endpoints are the frequency of patient discharges from the Emergency Department with a sinus rhythm and the frequency of successful cardioversion to a sinus rhythm within 24 h. All adverse effects, including extracardiac, will be assessed and categorized based on their severity, type and frequency. Table 3 lists all the study primary and secondary endpoints.

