In our recent meta-analysis [17], 473 patients with ischemic cardiomyopathy or heart failure were included and the effectiveness and safety profile of the class IC agents for the cardioversion of PAF was examined. The results showed that intravenously administered flecainide is the most effective choice for the pharmacologic cardioversion of atrial fibrillation, as only two patients needed to be treated in order to cardiovert one within 4 h. Only one patient exhibited ventricular arrhythmia in a 1992 study, 6% of patients demonstrated hypotension and 0.9% bradycardia. In studies that followed (prior to 2004), and are even referenced in the latest ESC guidelines, no episode of ventricular tachycardia was recorded. Similar results were found at the propafenone group. These findings could demonstrate that ischemia, and not the presence of structural heart disease, may be the culprit for the increased risk associated with class IC agents for the cardioversion of AF. 

In a recent retrospective study, 3445 patients receiving a class IC agent were compared to 2216 patients under sotalol or dofetilide, in a time span of 16 years [25]. The patients had variable degrees of coronary artery disease but no history of ventricular tachycardia, ICD or non-revascularized myocardial infarction. The authors found that IC agents are not associated with an increased mortality in certain patient groups that these drugs are currently restricted in, such as select patients with nonobstructive CAD without a history of VT. 

While designing the trial, patient safety was our utmost priority, and we incorporated a slew of strategies to minimize the risk for patients. First, this is evidenced by the stricter implementation of the ESC guidelines regarding residual ischemia. More specifically, in case of a CABG procedure, we required the date of the surgery to be within the last 3 years instead of 5 years. Secondly, we excluded all patients with suspicious symptoms resembling an acute coronary syndrome and we enrolled patients with a negative high-sensitive troponin result. As an extra layer of precaution, following enrolment and intervention initiation, all patients without suspicious symptoms were assessed using a second measurement of high-sensitivity troponin at 1 h. 

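### Safety non-inferiority is a primary goal, but the article states no margin, expected rate, power or decision rule for it; its only margin and power concern cardioversion

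*Protocol article*

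**What the plan says.** Section 2 (Objectives) of the protocol article sets two primary goals of different kinds. For efficacy the goal is "to prove the superiority of flecainide over amiodarone in the successful cardioversion of paroxysmal atrial fibrillation at the Emergency Department". For safety it is "to prove that the safety of flecainide is non-inferior to amiodarone in patients with coronary artery disease without residual ischemia". Section 3.7 and Table 3 list two matching primary endpoints: cardioversion within 6 h, and "the combined frequency of PVCs, NSVT, SVT, bradycardia and hypotension during the same time frame".

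Section 3.4 is the only sample-size text, and it deals with cardioversion alone. Its inputs are pooled rates: "we estimated the pooled cardioversion rate by flecainide within 4 h 65% whereas by amiodarone 23" per cent. Its only margin is also on that rate. Flecainide counts as non-inferior "if the lower margin of the confidence interval does not go lower than the pooled rate (65%) by more than 20" per cent, that is, not below 45%. The result is that "a sample size of 96 patients per arm is required to achieve 80% power to demonstrate the efficacy of flecainide", with 100 per arm to be recruited.

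Section 3.8 plans descriptive summaries, an intention-to-treat analysis with per-protocol sensitivity analyses, and, if an interim analysis is held, a threshold of 0.03 at both the interim and the final analysis. It gives no non-inferiority criterion for safety. The only rates in the article that bear on the composite are background figures in the Discussion, from a meta-analysis of class IC agents: "6% of patients demonstrated hypotension and 0.9% bradycardia".

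**The concern.** A non-inferiority claim is defined by its margin. Without one there is no null hypothesis to reject and no way to say whether the sample is large enough. Here the article prints a margin and a power statement, but attaches them to the endpoint whose stated goal is superiority. The endpoint whose stated goal is non-inferiority has neither.

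The Discussion describes class IC agents as contraindicated for cardioversion in coronary disease after revascularization, and section 3.1 says that the trial is meant to fill that gap, so the safety comparison is central. Section 3.3 confirms that treatment is known to patients and researchers. In an open-label trial, a margin chosen after event rates have become visible can be fitted to the result. If no margin is fixed, an absence of statistical significance may be taken as support for the safety claim, which it is not.

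**Working it through.** **1. Reproducing the stated 96 per arm.** Inputs from section 3.4: 65%, 45% (65% minus 20 points), type I error 0.05, power 80%; 1:1 allocation from section 3.3. Two-sided comparison of two proportions, pooled variance under the null, mean rate 0.55:

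n = [1.96 × √(2 × 0.55 × 0.45) + 0.84 × √(0.65 × 0.35 + 0.45 × 0.55)]² / 0.20² ≈ 95.9, so 96 per arm.

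This matches exactly. Other readings do not:
- non-inferiority with both true rates 65% and a 20-point margin: 90 per arm (one-sided 0.025) or 71 (one-sided 0.05);
- superiority of 65% over 23%: 21 per arm;
- one-sample test of 65% against 45%: 48.

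No safety quantity enters the figure.

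**2. What 100 per arm can deliver on safety.** The article gives no composite rate, so the rates below are assumptions, as are a yes/no composite per patient, equal true rates p in both arms, and one-sided 0.025.

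- Standard error: SE = √(2p(1 − p)/100)
- 95% CI half-width: 1.96 × SE
- Smallest margin with 80% power: (1.96 + 0.84) × SE = 2.80 × SE

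| Assumed rate p | SE (points) | 95% CI half-width (points) | Smallest margin with 80% power (points) |
|---|---|---|---|
| 7% | 3.6 | 7.1 | 10.1 |
| 20% | 5.7 | 11.1 | 15.8 |
| 30% | 6.5 | 12.7 | 18.2 |
| 50% | 7.1 | 13.9 | 19.8 |

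The 7% row rounds 6% + 0.9% = 6.9% from the Discussion. It assumes that no patient had both events, applies a background class IC rate to both arms, and leaves out PVCs, NSVT and SVT, all of which are in the composite.

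Power for a 10-point margin at a 20% rate: Φ(0.10/0.0566 − 1.96) = Φ(−0.19) = 42%. At 30% it is 34%, and at 50% it is 29%.

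**3. Why non-significance is not enough.** Suppose 14% against 7% is observed with 100 per arm. The pooled rate is 10.5%, SE = √(2 × 0.105 × 0.895/100) = 0.0434, z = 0.07/0.0434 = 1.61, two-sided p ≈ 0.11. The observed rate has doubled, yet the difference is not significant. The upper 95% limit, with unpooled SE 0.0431, is 7 + 1.96 × 4.31 = 15.4 points. Whether that is acceptable depends entirely on the missing margin.

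**4. If the 0.03 final threshold applied to safety.** A two-sided 97% interval uses 2.17 in place of 1.96. At a 20% rate the 80%-power margin becomes (2.17 + 0.84) × 5.66 = 17.0 points, and power for a 10-point margin falls to Φ(1.77 − 2.17) = 34%.

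**The case against.** The article condenses protocol version 1.0, which is not shown, and an analysis plan may exist. A reader might infer that no safety margin exists anywhere; the documents support only that none is stated here. That limit stands. It does not dispose of the point, because the article does print a margin and a power statement, and puts them on the other primary endpoint.

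A reader might also infer that 200 patients are too few to show safety non-inferiority. The table does not support this. A margin near 20 points has 80% power at any event rate, and about 10 points is reachable if the rate is near 7%. What is missing is the decision rule and the stated power.

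Nor does section 3.8 prescribe reading a non-significant test as non-inferiority. Its 0.03 thresholds apply only if an interim is held, and section 3.4 shows that the authors know how to reason from a confidence limit. The misreading is a risk that the plan leaves open, not one that it instructs.

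It is also tempting to say that carrying the 20-point cardioversion margin over to safety would pass an observed 27% against 7%. It would not: the upper 95% limit is 20 + 1.96 × 5.12 = 30.0 points. Against 7%, the worst observed rate that passes is 17% (upper limit 18.9 points); 18% gives 20.04 and fails. The article does not propose that margin for safety in any case.

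Finally, the article does not say that the trial succeeds only if both primary endpoints are met. That is a design choice still to be stated.

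**Conclusion.** The point holds in this form: the article commits to proving safety non-inferiority as a primary goal but, as printed, gives no valid basis for concluding it. Margin, expected rate, power and confidence-interval rule are all unstated for the safety composite. The one margin and the one power statement belong to cardioversion, where section 3.4 speaks of non-inferiority and section 2 of superiority.

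On size, 100 per arm reaches 80% power for margins from about 10 points (7% event rate) to 19.8 points (50%). The low end rests on an event rate that omits the ventricular arrhythmia components. Counting PVCs under Holter monitoring may push the rate up, where tighter margins are underpowered; this is inference, since the article gives no rate. The arithmetic in step 1 is secure. The figures in step 2 are conditional on the assumptions listed there.

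**What to change.** Before any comparative data are seen:

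- State and justify an absolute risk-difference margin for the 6 h safety composite, with the expected rate.
- Conclude non-inferiority only if the upper limit of the two-sided 95% CI (flecainide minus amiodarone) lies below that margin. Use a 97% CI if the interim rule with its 0.03 final threshold is applied to safety.
- State the power that 100 per arm gives for that margin and rate.
- State whether overall success requires both primary endpoints.
- Reconcile the non-inferiority wording for cardioversion in section 3.4 with the superiority goal in section 2.

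If no justifiable margin is reachable with 100 per arm, replace the aim of proving non-inferiority with estimating the safety difference and its confidence interval.

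The cost is protocol and analysis-plan wording and one steering-committee decision. The drawback is that the stated safety aim may become less favourable.

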## 3. Materials and Methods

### 3.1. Trial Design Overview 

The FLECA-ED study [NCT05549752] is an ongoing, randomized, controlled, multi-center trial that aims to fill in the gaps relating to the use of flecainide for the cardioversion of AF in patients with a history of coronary artery disease without residual ischemia and a left ventricular ejection fraction > 35%. The trial’s start date was 24 March 2023, and the expected completion date is 1 November 2024. 

The trial population will be 200 consecutive all-comers to the emergency department with paroxysmal atrial fibrillation. These patients will be randomly assigned to the amiodarone or flecainide group, in a head-to-head comparison of the effectiveness and safety profile of the two drugs in this specific population. The study entails a baseline visit followed by the intervention visit (both at the ED), as well as one day follow-up at the investigation site for re-evaluation and a 30-day remote follow-up (phone visit). All eligible patients arriving at the ED that sign the informed consent and are enrolled in the trial will be fitted with a 24 h ECG halter device prior to drug administration in order to assess the incidence of PVCs, NSVT, SVT and bradycardia, as well as the time taken for cardioversion. For 6 h following the initiation of the drug administration, all the enrolled patients will stay at the Emergency Department under close monitoring. If the patient’s rhythm is not successfully restored to a sinus rhythm at 6 h, the patient will be admitted to the hospital and will receive intravenous amiodarone. 

This study will provide substantial data for the safety of flecainide in patients with coronary artery disease without residual ischemia. Furthermore, the direct comparison to amiodarone will demonstrate flecainide’s performance in terms of frequency and the time needed for successful cardioversion.

The FLECA-ED trial is being conducted in Emergency Departments in three large tertiary hospitals in Athens, Greece. Two hospitals (‘Hippokration’ and ‘Attikon’ General Hospitals) are public hospitals, while the third (Athens Heart Center) provides care only to privately insured patients. Each of these hospitals has a large daily influx of patients and a significant experience in research work. The trial is funded by WinMedica (Athens, Greece). All the participants in this study provide written, informed consent. All study personnel have training and certification in human subjects’ research. The whole study protocol is approved by the Hospitals’ Institutional Review Board, the National Organization for Medicines and National Ethical Committee. The authors take sole responsibility for the design and conduct of this trial, the analyses and the composition of this design paper and its contents.

### 3.2. Eligibility Criteria

Patients are eligible if the duration of paroxysmal atrial fibrillation is less than 48 h at the time of cardioversion or less than 7 days with usage of NOACs for more than 30 days at the time of cardioversion. Atrial fibrillation will be confirmed with a standard 12 lead electrocardiogram (ECG). Patients will be included only if they meet strict criteria that ensures that residual ischemia is not present. More specifically, only patients with a 1 year history of PCI or 3 year history of CABG will be included. If this criterion is not met, the patients must have a negative imaging-based stress test within the previous year. Patients exhibiting angina or similar symptoms at the ED will be excluded, as is the case for patients with a history of acute coronary syndrome within the last year. Patients are eligible regardless of their EHRA symptom classification score. Patients with a history of thyroid dysfunction are not excluded. Table 1 lists the inclusion and exclusion criteria for the trial enrolment.

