#### 3.5.1. Screening Phase (Vscr, Emergency Department)

In Vscr, the site staff will assess eligibility according to the inclusion and exclusion criteria and obtain written informed consent. The informed consent and the whole study protocol is approved by the National Ethics Committee. Patients signing the informed consent will also explicitly consent to telephone calls by the investigators for follow-ups. A dated copy of the signed informed consent will be given to the patient. The enrolment of the participants will be considered valid once they have given their consent, completed the screening process and are deemed eligible. The moment of inclusion is defined as when the patient signs and dates the informed consent form. Any assessments and examinations related to the study are conducted after the informed consent has been obtained. Patients who sign the informed consent form also explicitly consent to telephone calls from the investigators for ongoing follow-ups.

At the ED, all patients are under continuous ECG monitoring. Once the signed informed consent has been obtained, all patients are fitted with a 24 h ECG holter monitoring device, without a removal of the ED ECG monitor. The flowchart of a patient’s baseline assessments is shown at Figure 1.

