#### 3.5.2. Intervention Visit (V0)

The intervention visit is defined as the time at which the study staff intravenously administers the assigned drug and coincides with the screening visit. The drug that will be administered to each patient will be determined randomly, through a simple randomization process, as detailed in the relevant section. Patients in both groups will remain at the ED for a total of 6 h after starting the treatment, regardless of cardioversion status. If no adverse events occur during this time, including an AV block, sinus bradycardia < 50 bpm, syncope, presyncope, or systolic blood pressure < 90 mmHg and a cardioversion to sinus rhythm is successful, the patient will be discharged. Otherwise, the patient will be admitted to the hospital. Patients receiving flecainide with an unsuccessful cardioversion at 6 h will be hospitalized and receive amiodarone. Patients with an unsuccessful drug cardioversion after 24 h will undergo electrical cardioversion, according to the clinical judgment of the attending physician. All patients (i.e., those who were discharged at 6 h following a successful cardioversion and those who were hospitalized) will be under continuous 24 h ECG halter monitoring. The hospitalized patients will also be under continuous ECG monitoring until the time of a cardioversion. The 24 h ECG halter will be removed at 24 h from drug administration initiation, regardless of the cardioversion status.

In case of hemodynamic instability during or after the administration of the drug, or if the Δ (troponin at 1 h) is above the limit of the hospital’s laboratory troponin cut-off levels, the administration of the drug will cease, and the patient will be treated according to the guidelines. At discharge, the administration or non-administration of other medication will follow the guidelines, with the exception that patients will not receive treatment with a class Ic antiarrhythmic agent. 

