**Figure 2 jcm-12-03961-f002:**
[figure not shown]
Intervention visit flowchart.

**Table 1 jcm-12-03961-t001:** Eligibility criteria.

Inclusion Criteria
1. Age: 18–85 years old 2. Paroxysmal Atrial Fibrillation, documented by 12-lead ECG, with one of the following: a. Atrial Fibrillation onset less than 48 h from the time of presentation to the Emergency Department b. Atrial Fibrillation onset between 48 h and 7 days from the time of presentation to the Emergency Department and if patient has been on anticoagulation for at least 30 days c. History of Coronary Artery Disease without residual ischemia, defined by one of the following criteria: ▪ PCI ≤ 1 year, or ▪ CABG ≤ 3 years, or ▪ Negative imaging-based stress testing within 1 year, and: ▪ History of known coronary artery stenosis > 60% without revascularization, or ▪ PCI ≥ 1 year, or ▪ CABG ≥ 3 years 3. Ejection Fraction > 35% (documented by cardiac ultrasound at the Emergency Department, or within 1 year) 4. Signed informed consent from the patient or legal representative.

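### Section 3.2 and Table 1 time the AF-duration limit differently (cardioversion versus ED presentation) and differ on anticoagulation, so Table 1 admits some patients whom section 3.2 excludes

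*Protocol article*

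**What the plan says.** Section 3.2 (Eligibility Criteria) opens with the rule "Patients are eligible if the duration of paroxysmal atrial fibrillation is less than 48 h at the time of cardioversion". Its alternative is "less than 7 days with usage of NOACs for more than 30 days at the time of cardioversion". Both limits are tied to cardioversion, and only NOACs count. The abbreviation list defines these as novel oral agents.

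Table 1 starts the clock elsewhere. Inclusion item 2a reads "Atrial Fibrillation onset less than 48 h from the time of presentation to the Emergency Department". Item 2b reads "Atrial Fibrillation onset between 48 h and 7 days from the time of presentation to the Emergency Department", on condition "if patient has been on anticoagulation for at least 30 days". No anticoagulant class is named.

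Section 3.2 ends with a pointer: "Table 1 lists the inclusion and exclusion criteria for the trial enrolment". It does not say which text prevails where they differ, and no exclusion criterion in Table 1 closes the gap.

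On timing, section 3.5.2 says that the intervention visit "coincides with the screening visit". Section 3.5.1 adds: "Any assessments and examinations related to the study are conducted after the informed consent has been obtained".

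**The concern.** Both versions make AF duration, combined with prior anticoagulation, a gate for cardioversion: beyond 48 h, each asks for about 30 days of anticoagulation. They differ on three things: the moment at which duration is measured, the class of anticoagulant, and whether exactly 30 days is enough. The third is trivial in practice. The first two can give the same patient two different answers.

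The moment of measurement is the one that counts. If sites follow Table 1 as written, a patient without anticoagulation can be eligible on arrival and yet start the drug after 48 h, which section 3.2 does not allow. With three sites enrolling, two readings of one criterion also invite uneven enrolment and disputes over who is an eligibility deviation in the per-protocol sensitivity analyses of section 3.8.

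**Working it through.** **Reading used.** The time of cardioversion is taken as the start of study drug, because that can be applied at screening. Taken as actual conversion, the time is unknown at enrolment and falls later still, so the gap would be wider.

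**Notation.** Let *p* be AF duration in hours at ED presentation and *d* the delay in hours from presentation to drug start. Seven days is 7 × 24 = 168 h.

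| | Section 3.2 | Table 1, items 2a/2b |
|---|---|---|
| Short limb | *p* + *d* < 48 | *p* < 48 |
| Long limb | *p* + *d* < 168, NOAC for > 30 days | *p* from 48 to 168, any anticoagulation for ≥ 30 days |

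**Direction.** Since *d* ≥ 0, *p* + *d* < 48 implies *p* < 48. Likewise, *p* + *d* < 168 with a NOAC for more than 30 days implies either *p* < 48 (item 2a) or *p* between 48 and 168 with enough anticoagulation (item 2b). So, boundary values aside, everyone eligible under section 3.2 is eligible under Table 1, and all disagreement runs the other way. A grid of illustrative values (*p* from 1 to 199 h, *d* from 0 to 6 h, three anticoagulant states, five treatment durations) agrees: 2625 points are eligible under Table 1 only and 0 under section 3.2 only. Those counts reflect the chosen grid and show direction, not frequency.

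**Test patients.**

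| Patient | Section 3.2 | Table 1 |
|---|---|---|
| 1. *p* = 47, *d* = 2, no anticoagulant (49 h at drug start) | out | in |
| 2. *p* = 72, *d* = 2, vitamin K antagonist for 60 days | out | in |
| 3. *p* = 167, *d* = 2, NOAC for 60 days (169 h at drug start) | out | in |
| Control: *p* = 20, *d* = 2, no anticoagulant | in | in |
| Control: *p* = 72, *d* = 2, NOAC for 60 days | in | in |

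**Is *d* above zero?** Screening and intervention form one visit, but several steps come before the drug: consent, fitting the Holter device (section 3.1), a negative troponin result for enrolment (section 4), and the chest X-ray and laboratory tests that Table 2 puts at screening. Table 2 marks the eligibility check at screening only.

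**Size of the window.** The article gives no value for *d*; 0.5 to 4 h is an assumption.

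- Short limb: the conflict starts at *p* = 48 − *d*, which is 47.5 h for *d* = 0.5, 47 h for *d* = 1 and 44 h for *d* = 4.
- Width relative to the 48-h range: 0.5/48 = 1.0% to 4/48 = 8.3%.
- A patient arriving at 47 h is at 47 + 0.5 = 47.5 h to 47 + 4 = 51 h when the drug starts, and reaches 48 h once *d* is 1 h or more.
- Long limb: 168 − 0.5 = 167.5 h to 168 − 4 = 164 h.

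**The case against.** The best defence is that section 3.2 points to Table 1 as the list of criteria, so the table is the operative text and the prose is a loose lead-in. Because the rules are nested, a site that applies both simply gets the stricter one; nothing is unworkable. The full protocol (version 1.0) and Figure 1 are not shown and may already hold a single rule.

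Much of this stands. It limits how far the point can go, but it does not remove the conflict. A condensed article may leave detail out; here it states two different limits. And if Table 1 governs, that is the version which lets a patient without anticoagulation pass 48 h before treatment.

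Three stronger readings are tempting and not supported:

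- *That the trial's power or primary comparison is compromised.* Nothing in the article shows this. Eligibility is settled before 1:1 allocation, and the number affected is unknown.
- *That 1.0% to 8.3% of patients are affected.* Those figures are widths of a time window under an assumed delay. The article gives no distribution of onset times, and its Introduction says that most AF patients in the cited ED data were already anticoagulated.
- *That coronary disease is optional because Table 1 shows it as item 2c among alternatives.* This may be table layout, and exclusion 3 keeps coronary disease mandatory.

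**Conclusion.** The inconsistency is real and the point holds in a limited form: one eligibility threshold is stated in two ways, and Table 1 is the broader. Only the first test patient bears on the safeguard that both versions set; the other two are anticoagulated, and no safety harm is claimed for them. The number of patients is probably small and cannot be derived from the article. The conclusion rests on reading the time of cardioversion as drug start and on some delay between arrival and drug, which the listed steps make near certain; the 0.5 to 4 h range only illustrates its size. Whether sites actually face the ambiguity cannot be known without the full protocol.

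**What to change.** State one rule in both section 3.2 and Table 1: AF of less than 48 h at study-drug initiation, or less than 7 days at study-drug initiation with at least 30 days of anticoagulation. Keep Table 1's anticoagulant wording, and check the rule in the eCRF before randomisation, using the expected time of drug start.

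The cost is amendment wording and one eCRF check, applied from the amendment onward because enrolment began on 24 March 2023. A few patients who cross the 48-h or 7-day limit during screening become ineligible. Keeping Table 1's anticoagulation wording loses no one on that condition; restricting it to NOACs would. If the full protocol already uses one rule, no amendment is needed and the article should be corrected to match it.
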